#### Inclusion and exclusion criteria

All patients between 12–18 years of age, with fully erupted permanent dentition, and who are scheduled for treatment with full fixed appliances, will be eligible to participate in this study.

Exclusion criteria are as follows:Patients younger than 12 years of age, since they generally do not have fully erupted dentition, and patients older than 18 years of age, since the risk of WSL development is reduced after this agePatients diagnosed with bronchial asthma, due to the use of fluoride varnish (Duraphat 50 mg/mL; Pharbil Waltrop GmbH, Germany, RVG 10942)Patients with physical or mental problems that make them incapable of practicing proper oral hygienePatients who refuse to use the prescribed preventive productsPatients with missing incisors, canines, and/or premolars, since these are the teeth scored for outcome assessment.Patients with cleft lip and palate or craniofacial anomalies, since different preventive strategies are needed for these patients.

#### Sample size and power calculation

We have calculated the number of patients needed to detect a difference in the proportions of patients with newly developed or enlarged WSLs between the intervention group using the CPG and the control group using standard preventive strategies. Earlier studies show that more than 1 in 4 orthodontic patients develop at least one new WSL during the course of orthodontic treatment [3]. Assuming a power of 80 %, a significance level of 5 %, and an ICC of 0.05 to correct for clustering, we calculated that we must include a minimum of 14 orthodontic practices with 50 patients per practice to detect a medium effect size of 0.4 for reduction in newly developed WSLs. The effect size was arbitrarily chosen, as no previous data establish what would constitute a clinically relevant change. The study is powered to detect an effect of 15 % absolute reduction in prevalence of WLS, under the assumptions specified above. Assuming a drop-out rate of 20 %, we plan to recruit a total of 60 patients per participating practice, resulting in a total inclusion of 840 patients. In a regular orthodontic practice, about 40 patients receive full fixed appliances each month. To account for an overestimation of the number of patients to potentially be included in the practices, we will have a 2-month inclusion period.

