#### Primary outcome

To account for the data clustering (in orthodontic practices), a multilevel logistic regression analysis will be applied on patient data, using the presence of new WSLs at T2 (yes/no) as the outcome, and the type of intervention (CPG or usual preventive measures) as the predictor. In this model, the regression coefficient of the predictor “intervention versus control” indicates the effectiveness of the intervention. Given the expected distribution of outcomes, we anticipate the use of binomial logistic regression with a logit link function. We will also examine the influences of age at start of treatment, gender, patients’ opinion on preventive measures, patients’ initial oral health status, patients’ initial oral hygiene status, and patients’ initial sugar intake on the primary outcome measure, by including these factors one by one as predictors in the regression model. These covariates are known to potentially influence the development of WSLs during orthodontic treatment [3, 9]. We do not anticipate a high number of missing values. However, in the event that we do have high numbers of missing values, we will apply a multiple imputation method prior to the planned analyses.

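### Sample size: 60 per practice leaves 48, not the stated minimum of 50, after 20% drop-out; separately, 80% power with 14 practices ignores the small number of clusters and is about 74–75% on 12 degrees of freedom

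*Protocol article*

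**What the plan says.** The section on sample size and power lists its assumptions as "Assuming a power of 80 %, a significance level of 5 %, and an ICC of 0.05 to correct for clustering". From these, "we calculated that we must include a minimum of 14 orthodontic practices with 50 patients per practice", in order "to detect a medium effect size of 0.4 for reduction in newly developed WSLs". The same section equates this with an absolute effect: "The study is powered to detect an effect of 15 % absolute reduction in prevalence of WLS". The control rate is given only as more than one patient in four. For an assumed 20% drop-out, "we plan to recruit a total of 60 patients per participating practice", 840 patients in all.

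Randomisation is by practice (Randomization section). For the primary outcome, the Statistical analysis section says that "a multilevel logistic regression analysis will be applied on patient data", with the intervention coefficient as the measure of effect. It does not name the test, the estimation method or the reference distribution.

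**The concern.** Two figures in the sample size section do not follow from the inputs beside them.

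- **Recruitment.** Multiplying the required number by 1 + 0.20 does not protect it against a 20% loss; dividing by 1 − 0.20 does. The plan therefore misses its own minimum under its own drop-out rate.
- **Power.** The design effect allows for correlation within practices, but not for estimating the between-practice variance from only 14 practices. With 7 per arm, a comparison that respects the randomised unit has 14 − 2 = 12 degrees of freedom and a critical value of 2.18 instead of 1.96.

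At stake is whether the trial has the power it states. There is also the question of which reference distribution the primary test will use, since the sample size method gives no sign that the number of practices was considered.

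**Working it through.** **Inputs stated in the article:** power 80%, significance level 5%, ICC 0.05, effect size 0.4, absolute reduction 15 points, 14 practices of 50, drop-out 20%, 60 recruited per practice.

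**Assumptions (not stated):** two-sided level, 7 practices per arm, equal practice sizes, control rate 25%. At 25% v 10% the arcsine effect size is 0.404, so 0.4 and 15 points then agree.

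**1. Reproducing the 14 practices.**
- Individually randomised number per arm: 2 × (1.96 + 0.842)² / 0.4² = 98.1, so 99. The two-proportion formula for 25% v 10% gives 100.
- Design effect at 50 per practice: 1 + 49 × 0.05 = 3.45.
- Practices per arm: 99 × 3.45 / 50 = 6.83, or 100 × 3.45 / 50 = 6.90. Both round up to 7, which is 14 in total. The stated figure reproduces with a normal critical value.

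**2. Drop-out.**
- 60 × 0.8 = 48 per practice; 840 × 0.8 = 672, against 14 × 50 = 700.
- 50 / 0.8 = 62.5, so 63 per practice and 14 × 63 = 882.
- 60 per practice covers 1 − 50/60 = 16.7% drop-out.

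**3. What the drop-out slip costs by the plan's own method.**
- At 48 the design effect is 1 + 47 × 0.05 = 3.35, and the practices needed are 99 × 3.35 / 48 = 6.91 or 100 × 3.35 / 48 = 6.98: still 7 per arm.
- Normal-approximation power is 80.8–82.0% at 50 and 80.3–81.6% at 48, depending on the effect metric. The loss is about 0.5 point.

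**4. Power with 12 degrees of freedom.** Effective number per arm = 7m / design effect; noncentrality = 0.4 × √(effective number / 2).

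| Evaluable per practice | Effective n per arm | Noncentrality | Power, normal | Power, t on 12 df |
|---|---|---|---|---|
| 50 | 350 / 3.45 = 101.4 | 2.849 | 81.3% | 74.4% |
| 48 | 336 / 3.35 = 100.3 | 2.833 | 80.9% | 73.9% |

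Over the other effect metrics (25% v 10% as a difference in proportions, or 0.404), the t-based figures are 75.0–75.2% at 50 and 74.5–74.7% at 48. A simulation of 4,000 trials (beta-binomial, ICC 0.05, 7 practices of 48 per arm) gave a practice-level t-test 74.6% power at 25% v 10%, and 4.3–4.8% type I error.

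With 12 degrees of freedom, 80% power is reached at a drop of about 15.8 points (25% to 9.2%). Keeping 15 points would take 8 practices per arm (80.4–80.9% at 48 per practice).

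**5. Sensitivity to the control rate.** For the same 15-point drop at 48 per practice, t-based power is about 66% at 30% v 15% (normal: about 73%) and about 56% at 40% v 25%.

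**6. Conditional check of the primary model.** The random-intercept logistic model was fitted by maximum likelihood to the same simulated trials, 48 per practice:

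| Test | Type I error | Power, 25% v 10% |
|---|---|---|
| Wald z, uncorrected | 8.7–9.0% | 85.2% |
| Likelihood ratio | 7.0–7.3% | 82.2% |
| Wald with t on 12 df | 6.1% | 79.6% |

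The power figures in this table go with type I error above 5%.

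**The case against.** The strongest reply is that the headline figure is sound by its own method: 14 practices of 50 follow from the stated inputs, the normal approximation with a design effect is in common use, and the effect size was chosen arbitrarily by the article's own account, so a move from 15 to about 16 points changes little clinically. That the figure reproduces is true. It does not rescue the 80%, because with 12 degrees of freedom the approximation overstates power by about 7 points.

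Three stronger readings are tempting and should not be drawn.

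- A reader might infer that the drop-out slip causes the power shortfall. It does not: 48 per practice keeps normal-approximation power above 80%, and a full 50 still gives only 74–75% on 12 degrees of freedom. The shortfall comes from the number of practices.
- A reader might infer that the plan prescribes a Wald z-test and so has an inflated type I error. The article names a model and a coefficient, not a test, and the choice may lie in an analysis plan that is not shown. The inflation is a conditional risk.
- A reader might infer that the only choices are about 75% power or roughly double the stated error rate. The likelihood-ratio test and the Wald statistic on 12 degrees of freedom fall in between.

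**Conclusion.** Both errors stand, and they are independent. The drop-out arithmetic is wrong whatever the analysis: 60 per practice gives 48 evaluable (672), against a stated minimum of 50 (700). Its effect on power is about 0.5 point.

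The stated 80% power holds only under a normal approximation. With a t reference on 12 degrees of freedom, power for 25% v 10% is about 74–75%, and 80% applies to about 16 points. This rests on the four assumptions listed above. The 25% control rate is a favourable one, since the article says the rate is higher than that.

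On type I error the conclusion is conditional only: about 9% with an uncorrected maximum-likelihood Wald z and about 7% with a likelihood-ratio test, against the stated 5%. Nothing in the article says that either will be used.

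**What to change.** 1. **Drop-out.** Either state that 60 per practice covers 16.7% drop-out and leaves 48 evaluable at 20%, or recruit 50 / 0.8 = 63 per practice (882). The first costs only wording; the second costs 42 more patients (882 − 840).
2. **Power.** Restate it as about 74–75% for a 15-point reduction, or 80% for about 16 points, and give the sidedness, allocation and control rate assumed. This needs no extra patients, but the stated power becomes less favourable. If 80% for 15 points is to be kept, about 16 practices are needed; the Trial status section reports that eight of the 14 were still being recruited.
3. **Primary test.** Name a method suited to 14 clusters: a practice-level t-test on 12 degrees of freedom, or the multilevel logistic model with Kenward-Roger or a similar small-sample degrees-of-freedom correction (for Kenward-Roger, fitted by restricted pseudo-likelihood). Putting 12 degrees of freedom on a maximum-likelihood Wald statistic helps but still gave 6.1% in simulation. The cost is one model option and a sentence; if an analysis plan already specifies this, a cross-reference is enough.

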### Preventive intervention

The intervention involves the implementation of a CPG for WSL prevention prior to and during orthodontic treatment with fixed appliances (Fig. 1 and Table 1). The CPG has been converted into a CDSS that indicates the appropriateness of starting, postponing, or ending orthodontic treatment and/or of undertaking additional preventive measures during treatment. These decisions are based on the patient’s initial caries risk, as determined based on oral health status, oral hygiene status, and sugar intake. These factors will be assessed by the clinician during regular orthodontic check-up visits, which generally occur every 4–6 weeks. Based on the patient’s individual caries risk prior to orthodontic treatment, a decision will be made regarding whether to start or postpone orthodontic treatment. During orthodontic treatment, the same caries risk assessment will be used to determine whether the patient requires 1) appropriate oral hygiene instruction, 2) appropriate oral hygiene instruction and fluoride varnish application, or 3) removal of orthodontic appliances. The CPG also recommends that the orthodontist inform parents and referring dentists about the oral health situation and the possible implications for treatment.

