**Fig. 1 Fig1:**
[figure not shown]
Clinical practice guideline. Abbreviations are defined in Table 1

**Table 1 Tab1:** Abbreviations used in the clinical practice guideline

General preventive measures/recommendations prior to orthodontic treatment with fixed appliances	Abbreviation
1. The mouth should be free of plaque, caries, and gingivitis before starting orthodontic treatment	GM1-7
2. Explanation of the current oral health situation	
3. Advice regarding tooth-friendly nutrition and oral hygiene	
4. Oral hygiene instruction, evaluation of psychomotor skills and, when appropriate, advise brushing with powered tooth brush	
5. Topical fluoride varnish on visible/present white spots	
6. Tooth brushing with toothpaste containing fluoride (1,450 ppm) twice daily	
Start treatment when oral health status is appropriate	ST
Postpone treatment until specific requirements are met, as stated in the general measures/recommendations, including appropriate oral hygiene level and lower risk of caries due to decreased sugar intake	PT
Specific preventive measures/recommendations during orthodontic treatment with fixed appliances	
Use of a toothpaste containing fluoride (1,450 ppm) twice daily	HF
Removal of the wires, cleaning/polishing the teeth, and applying topical fluoride varnish	FV
Appropriate dietary and oral hygiene advice	DA
Letter to the (parents of the) patient including an explanation of the problem and a copy to the GDP	LP1
Letter to the (parents of the) patient describing visible carious damage to the teeth, including an explanation of the problem and a copy to the GDP	LP2
Letter to the (parents of the) patient regarding debonding (removal of all fixed appliances) with a copy to the GDP	LP3
Debonding (removal of all fixed appliances without placement of permanent retention)	DB

The CPG has been converted into a CDSS, which is to be integrated in the electronic patient files (EPFs) of the participating practices. For each patient, the program will automatically lead the clinician through the questions needed to determine the patient’s caries risk. Upon input of the answers, the program will display the recommended preventive strategy to be followed, and will store all of this information in the EPF.

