The control group will not receive any intervention. Practices in the control arm of the trial will use their standard WSL preventive measures. Registration in the EPF will be performed in accordance with the medical record keeping guidelines of the Dutch Dental Society [12].

Pre- and post-treatment digital intra-oral photographs will be taken in both the intervention and the control practices. The photographic setting will be standardized in terms of lighting conditions and camera positioning to ensure validity of the WSL measurements [13].

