### Outcome parameters

#### Primary outcome

The primary outcome measure is the proportion of patients treated with full fixed orthodontic appliances who develop at least one new or enlarged WSL after 6–9 months of treatment with fixed appliances, and at the completion of treatment, when using the CPG for WSL prevention as compared to usual preventive measures.

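### The start/postpone decision, stated for the guideline arm only, can remove higher-risk patients from the primary comparison, and the protocol does not say how postponed patients are counted

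*Protocol article*

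**What the plan says.** All references are to the protocol article.

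- **Order of events.** Table 3 (Data collection) assigns practices in month 3 and starts patient inclusion in months 4–6. The participating orthodontists recruit (Patients).
- **Guideline arm.** Preventive intervention: from each patient's caries risk before treatment, "a decision will be made regarding whether to start or postpone orthodontic treatment". Table 1 describes postponement as "Postpone treatment until specific requirements are met, as stated in the general measures/recommendations", and gives no time limit.
- **Control arm.** Preventive intervention: "Practices in the control arm of the trial will use their standard WSL preventive measures". No start/postpone rule is stated.
- **Entry.** Inclusion and exclusion criteria: patients aged 12–18 who are "scheduled for treatment with full fixed appliances, will be eligible to participate in this study". The guideline-arm information forms part of the consent obtained at the treatment-plan discussion (Patients). Sample size and power calculation: "we will have a 2-month inclusion period", with 60 patients per practice and about 40 starts per month.
- **Denominator.** Outcome parameters, Primary outcome: "the proportion of patients treated with full fixed orthodontic appliances who develop at least one new or enlarged WSL".
- **Timing.** The section on patients' experience with preventive strategies puts the first and last included patients at about 6 and 4 months of treatment when 6 months have passed since first inclusion. Intra-oral digital photographs ties T1 and T2 to each patient's own treatment; Table 3 gives calendar months for both.
- **Safeguards.** Recruiters receive instructions against selection bias, whose content is not given. The Statistical analysis section adds initial oral health, hygiene and sugar intake to the model singly.

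**The concern.** Allocation is known when patients are recruited, and one arm then applies a risk-based decision before appliances are placed. The article does not say whether a patient is counted as enrolled before or after that decision, or what happens to an enrolled patient who never starts. If postponed patients go uncounted, the guideline arm is left with a lower-risk group than the control arm. The guideline could then show fewer patients with white spot lesions even if its preventive measures had no effect, and the error would run in the direction of the trial's hypothesis. Patients who were never enrolled cannot be recovered by any later analysis.

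**Working it through.** **1. The plan's own figures.** Inputs from Sample size and power calculation: 25% control risk, 15-point reduction (to 10%), 80% power, 5% significance (two-sided assumed), ICC 0.05, 50 patients per practice.

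- The two-proportion formula gives 100 per arm.
- Design effect = 1 + (50 − 1) × 0.05 = 3.45, so 345 per arm.
- 345 / 50 = 6.9, hence 7 practices per arm and 14 × 50 = 700, as stated.
- Cohen's h for 25% against 10% is 0.404, matching the stated 0.4.

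So 25% and 15 points are a fair yardstick.

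**2. Does the schedule allow for a delay between inclusion and bonding?**

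- T1: inclusion in months 4–6 plus 6–9 months of treatment gives 4 + 6 = 10 to 6 + 9 = 15. Table 3 shows 10–15, with no slack.
- Patient questionnaire: 6 and 4 months of treatment at 6 months after first inclusion means the last patient, included 2 months later, started on inclusion.
- T2: starts in months 4–6 plus 24–30 months of treatment give months 28–36, against 22–30 in Table 3. This mismatch affects both arms.

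**3. Can a practice fill its quota after postponing patients?** Two months at 40 per month give 80 candidates for 60 places. 1 − 60/80 = 25%, so a guideline practice could postpone up to a quarter of its candidates and still reach 60.

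**4. Possible size, with no true effect.** Let s be the share of higher-risk patients and k their risk relative to the others. Both are assumptions; the documents give neither. With 25% overall, the lower-risk group has p = 0.25 / (1 − s + s·k). If all higher-risk patients are lost from the guideline arm, its rate is p. If a fraction f is lost, the share left is s′ = s(1 − f) / (1 − s·f) and the rate is p(1 − s′) + k·p·s′. False-positive rates use a normal approximation with an effective 350 / 3.45 = 101 per arm.

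| s | k | Rate, all lost | Spurious difference | False-positive rate | Difference, half lost | False-positive rate, half lost |
|---|---|---|---|---|---|---|
| 10% | 1.5 | 0.25/1.05 = 23.8% | 1.2 points | 5.4% | 0.6 points | 5.1% |
| 20% | 2 | 0.25/1.20 = 20.8% | 4.2 points | 10.9% | 1.9 points | 6.1% |
| 30% | 3 | 0.25/1.60 = 15.6% | 9.4 points | 38.2% | 3.9 points | 10.0% |

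The last row exceeds the 25% that replacement within the quota can absorb. At s = 25% and k = 3 with all lost, the difference is 25.0 − 16.7 = 8.3 points.

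**5. Scoring never-bonded patients as free of lesions.** Let s be the share never bonded and r the risk they would have had (both assumed). Leaving them out gives (0.25 − s·r)/(1 − s). Keeping them as lesion-free gives 0.25 − s·r.

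| s | r | Left out | Spurious difference | Scored lesion-free | Spurious difference |
|---|---|---|---|---|---|
| 10% | 40% | 23.3% | 1.7 points | 21.0% | 4.0 points |
| 15% | 50% | 20.6% | 4.4 points | 17.5% | 7.5 points |
| 20% | 60% | 16.3% | 8.8 points | 13.0% | 12.0 points |

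Retaining these patients with that score makes the distortion larger.

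**The case against.** The strongest reply is that, read literally, enrolment comes first. Eligible patients are scheduled for treatment, guideline-arm consent belongs to the treatment-plan discussion, and the two months are an inclusion period, not a bonding deadline. A reader might infer that entry requires bonding within two months; the criteria do not say so. This stands as a limit on the point but does not remove it. A patient enrolled and then postponed indefinitely still falls outside a denominator of treated patients, and the calendar makes no allowance for the delay.

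Other strong readings also go beyond the text:

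- **That comparable control patients all start at once.** Usual care may include postponement; the article only states no rule for it.
- **That Table 3 cuts late starters off.** The photograph section follows each patient's own treatment, and a hard T2 cut-off would lose patients in both arms.
- **That a patient-level randomisation is broken.** Randomisation is by practice.
- **That any lower risk after postponement is bias.** Where the patient then starts, it is part of what the guideline is meant to achieve.

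The safeguards deserve credit but do not close the gap. The content of the recruitment instructions is not given. Risk factors are entered singly. The compliance section limits control-arm registration to oral health and hygiene at treatment start, so sugar intake, one of the three factors behind the decision, is not listed for controls. Imputation is reserved for high numbers of missing values and cannot restore patients who were never enrolled. An unseen full protocol may hold fuller enrolment rules, but the denominator and calendar are fixed in this article.

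**Conclusion.** The point holds as a route to selection after allocation that the protocol leaves open. It does not show that the arms will enrol populations of different risk. The direction is predictable: if the postponed patients who go uncounted carry above-average risk, and control practices do not lose similar patients, the comparison favours the guideline.

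The size cannot be derived from the documents. On the assumed shares and risk ratios it is about 1 to 9 points when every postponed patient is lost, at most a little over 60% of the 15-point target. When half are lost it is 0.6 to 3.9 points. If nearly all simply start later and keep their photographs, it becomes negligible. It is worth settling now: under Trial status, eight of the 14 practices are still being recruited, and enrolment losses cannot be repaired afterwards.

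**What to change.** 1. State that in both arms entry occurs at the treatment-plan discussion, before any start/postpone decision. Consecutive eligible, consenting patients count towards the 60 whatever that decision is.
2. Have each practice keep an enrolment log of patients assessed, enrolled, postponed, started and never started.
3. Reconcile Table 3 with the photograph section, so that T1 and T2 follow each patient's own treatment start and late starters keep both.
4. Define the primary analysis set as all enrolled patients, and align the wording of the primary outcome with it.
5. Report never-bonded patients by arm. Do not score them as lesion-free: treat the outcome as missing and impute it from baseline risk. Give sensitivity analyses that leave them out and that vary their imputed risk.
6. Record initial oral health, hygiene and sugar intake in both arms before the decision, and adjust for them jointly.

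The cost is somewhat more record-keeping, later photographs for some patients and possibly a smaller observed effect. Imputation also assumes that the recorded baseline factors explain the risk of never-bonded patients, which is why the sensitivity analyses are needed. The clinical start/postpone rule is left unchanged.
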